## Abstract

**Background:**

Youth are an important target group for social network interventions, because they are particularly susceptible to the adaptation of healthy and unhealthy habits and behaviors of others. They are surrounded by ‘social influence agents’ (i.e., role models such as family, friends and peers) that co-determine their dietary intake and physical activity. However, there is a lack of systematic and comprehensive research on the implementation of a social network approach in health campaigns. The *MyMovez* research project aims to fill this gap by developing a method for effective social network campaign implementation. This protocol paper describes the design and methods of Phase I of the *MyMovez* project, aiming to unravel youth’s social network structures in combination with individual, psychosocial, and environmental factors related to energy intake and expenditure. In addition, the *Wearable Lab* is developed to enable an attractive and state-of-the-art way of collecting data and online campaign implementation via social networks.

**Methods:**

Phase I of the *MyMovez* project consists of a large-scale cross-sequential cohort study (*N* = 953; 8-12 and 12-15 y/o). In five waves during a 3-year period (2016-2018), data are collected about youth’s social network exposure, media consumption, socialization experiences, psychological determinants of behavior, physical environment, dietary intake (snacking and drinking behavior) and physical activity using the *Wearable Lab*. The *Wearable Lab* exists of a smartphone-based research application (app) connected to an activity tracking bracelet, that is developed throughout the duration of the project. It generates peer- and self-reported (e.g., sociometric data and surveys) and experience sampling data, social network beacon data, real-time physical activity data (i.e., steps and cycling), location information, photos and chat conversation data from the app’s social media platform *Social Buzz*.

**Discussion:**

The *MyMovez* project - Phase I is an innovative cross-sequential research project that investigates how social influences co-determine youth’s energy intake and expenditure. This project utilizes advanced research technologies (*Wearable Lab*) that provide unique opportunities to better understand the underlying processes that impact youths’ health-related behaviors. The project is theoretically and methodologically pioneering and produces a unique and useful method for successfully implementing and improving health campaigns.

**Electronic supplementary material:**

The online version of this article (10.1186/s12889-018-5353-5) contains supplementary material, which is available to authorized users.

## Background

Most Western societies devote substantial financial and human resources to the development and implementation of media health campaigns. The alarming rise of obesity has led to a particular increase in efforts aimed at the prevention and reduction of child and adolescent obesity. Youth are an important target group for health communication, because they are especially susceptible to environmental influences and because habits formed during this developmental period persist into adulthood. Unfortunately, media health campaigns often have a disappointing impact. Health messages may be successful in changing behaviors in a laboratory setting, but evaluation research consistently shows little impact in society [1].

An explanation for the gap between laboratory campaign design and behavioral adoption in society is that most mass media campaigns do not take into account the social context in which the message is received. The crucial role of the social environment on youth’s weight-related behaviors is increasingly recognized by academics, health practitioners, and politicians [2–5]. Youth are surrounded by family members, peers and other role models (i.e., *social influence agents*) who support and/or undermine the targeted behaviors. Not only do these social influences compete with media influences, they also play a crucial role in how media messages are transmitted, received, and evaluated. Especially peers are of critical importance when youth reach adolescence, and they play a crucial role in message processing [6]. Recent developments in the media landscape, in particular the explosive growth of social media, present a practical way to incorporate the social context in campaign implementation. Aside from advantages such as wide reach, low costs, and ample technological possibilities, social media enables to reach target recipients via their social networks [7].

Social network interventions make use of peer influence to change behavior throughout the social network [8]. Contrasting traditional mass health intervention campaigns in which *all* individuals are exposed to an intervention message, social network campaigns only target *influential* individuals to perform and stimulate specific behaviors. When social influence agents disseminate the appropriate behavior successfully, it is expected that the behavior will be incorporated by others within their social networks. Subsequently, a social network approach has potential to cause long-term behavior change when the behavior becomes incorporated as the group norm. The approach has been successful in improving health-related behaviors such as quitting smoking [9, 10], increasing condom use [11], and promoting water drinking [12]. However, despite their increasing popularity, it remains unclear how social network campaigns actually work and what are the most effective ways to implement them. Greater understanding of social network structures and social influence processes is crucial for the development of theory and evidence-based social network interventions.

The overarching aim of this 5-year research project is to develop and test a method for effective media health campaign implementation by targeting the most powerful influence agents in youth’s social networks. The *MyMovez* project focuses on two important behavior types of the energy balance equation (i.e., energy intake and expenditure): the consumption of snack foods and (sugar-sweetened) beverages and physical activity (PA). In this protocol paper, we describe the design and methods of the first Phase of the *MyMovez* project. Phase I focuses on two parallel trajectories: Part A investigates youth’s social network structures and youths’ positions within these networks; and examines how media, personal and social influences co-determine energy intake and expenditure. Specifically, the overall aim is to i) identify the most powerful influence agents and examine similarity of health behaviors in youth’s social networks, and to ii) investigate which factors determine youths’ network positions as well as their energy intake and expenditure. In Part B, the research technology *Wearable Lab* is developed to enable data collection (and the campaign implementation in Phase II).

During a period of 3 years, a large-scale cross-sequential cohort study is conducted (*N* = 953) along with several focus group studies. The main sample of the *MyMovez* project – Phase I exists of two age-cohorts (8-12 and 12-15 y/o) of children and adolescents at 21 primary and secondary schools throughout the Netherlands. The recruitment of schools and participants took place with the assistance of several Dutch Public Health Services (GGDs). The *MyMovez* project is funded by the European Research Council (ERC) and carried out by a multidisciplinary research team of the Behavioural Science Institute, Radboud University, Nijmegen, in the Netherlands.

### Part A: Unraveling youth’s social network structures and positions

This project uses approaches and theories centered around the influence of the social environment to investigate how social influence agents can be identified, the relative importance of selection and influence processes, and what distinguishes social influence agents compared to other peers (i.e., ‘followers’). Ample empirical studies have proven the strong influence of peers on young people’s consumption behavior and physical activity [13–15]. For example, studies showed that youth follow and model each other’s eating behavior and that peers set guidelines or ‘social norms’ for others’ food choice and intake [16, 17]. In addition, peer groups are found to play a role in shaping physical activity behavior and youth are more active when they are together with peers [15, 18]. Social network interventions integrate peer influence processes in their campaigns to change behavior throughout the social network [8]. Yet, more research is needed to unravel how social influence agents can be identified and selected.

To date no systematic examination has been conducted on the selection process of social influence agents in peer-driven intervention studies. For example, most research on social networks are based on selecting influence agents who receive the most ‘friendship’ nominations; however, it is unclear whether this selection method is justified in the context of energy intake and expenditure [17]. Selecting influence agents based on ‘advice’ or ‘respect’ nominations (or a combination between these questions) [19] might identify other persons holding influential positions in the network compared to friendship queries. Also, these types of questions can be regarded as general and not directed to specific health behaviors, whereas it might be more useful to ask specific nomination questions (e.g., ‘with whom do you talk about PA?’ or ‘who is modeled a lot for their eating behavior?’) to identify social influence agents that exert power on health behaviors. In addition, there are different ways of analyzing the position or ‘centrality’ of individuals within networks. For example, a person receiving the most nominations has a high ‘in-degree’ centrality. Although this method is commonly used, it might be that ‘closeness’ centrality is a more effective measure because it describes how long it takes to spread information from that person to others (i.e., it takes into account the shortest paths a health message has to travel to reach the entire network). Another option would be to focus on ‘betweenness’ centrality, which indicates whether a person is important for linking different individuals or subgroups/clusters of individuals [20, 21]. To determine which individuals are the ideal social influence agents for the targeted behaviors of the *MyMovez* project, the selection process of social influence agents is investigated by focusing on different network centrality measures and by examining traditional (advice, leadership, friendship, etc.) and specific nomination items with regard to communication strategies, energy intake and expenditure.

It is also essential to identify which factors determine a person’s network position and which determinants mediate or predict engagement in energy behaviors. For example, research has shown an important role of ingratiation with regard to social normative and modeling behavior [13, 14]. That is, people try to influence each other to become part of a group and to be liked by conforming to social norms or modeling behavior. However, not all individuals are equally susceptible in doing so. Therefore, psychological determinants related to affiliation purposes and uncertainty reduction are collected such as need to belong, fear of negative evaluation, self-esteem, and athletic competence [13]. Nevertheless, research has focused mainly on characteristics of the followers and less on those of the social influence agents. There are limited indications that socially warm persons exert larger social influence than persons acting cold and that social influence agents have leadership status [8, 22]. To examine the characteristics of the influencers, Phase I also examines factors such as opinion leadership, public individuation, pro-social behavior, and participants are asked to profile themselves by choosing seven personality traits that describe themselves best [8, 21, 23, 24]. In addition, information about the social and physical environment is gathered that co-determine youth’s network positions and health behavior such as socio-economic status, social support, accessibility and availability of foods, and PA facilities [25].

The *MyMovez* project also uses a combination of renowned approaches and theories that predict behavioral change and provide insights in the performance of health behaviors and dissemination in social networks. For example, the constructs of the widely used Theory of Planned Behavior (TPB) are examined. The TPB has the general idea that when people have a positive attitude toward behavior and their social environment is supportive while they also feel they are capable and in control of their behavior, their intention to perform the behavior will be strong [26]. Importantly, people often fail to carry out healthy behaviors despite their positive intentions to eat healthy and engage in physical activity [27]. Therefore, additional constructs contributing to young people actually carrying out targeted behaviors (e.g., motivation [28, 29], self-persuasion [30], injunctive and descriptive norms [31], social modeling and impression management [32, 33]) stemming from the Diffusion of Innovation Theory, Social Normative approach [34], Self-Determination Theory [28] and the Fogg Behavior Model [29]), are examined to deepen the understanding of youth’s energy intake and expenditure. These insights from Phase I will contribute to develop an effective social network campaign for Phase II.

### Part B: Development of the *Wearable Lab*

A practical and modern way to conduct large scale research among youth is via smartphones, because it is an efficient, low-cost and less time-consuming method compared to traditional paper-and-pencil questionnaires. In addition, objective measures of health and real-time data can be collected. Furthermore, the social context can be incorporated by facilitating communications via social network functionalities. Part B of this comprehensive research project develops the *Wearable Lab*, existing of a highly innovative smartphone-based research application (*MyMovez* app) connected to an activity tracker. The research technology enables examining youth’s social network structures together with energy balance-related behaviors, media consumption, socialization processes and psychosocial determinants of behavior. The smartphone and activity tracker jointly collect self-reported and objective data on daily randomized and fixed time points. Each participant receives the *Wearable Lab* during each data wave for a period of 7 consecutive calendar days including the weekend.

The *Wearable Lab* is developed in an ongoing iterative process by means of focus group sessions as well as evaluations via the *MyMovez* app during the data collection waves. In 2015, six focus group sessions were conducted at primary (*N* = 30; 10-11 y/o) and secondary schools (*N* = 27; 12-13 y/o); with groups of boys or girls only and one mixed group at each school. Discussions were videotaped and led by trained researchers, and involved topics such as likes and dislikes of health, research apps and wearables, the design and attractive functionalities or features of the app, wearables and behavior tracking, and the project name. Outcomes contributed to choosing the name ‘*MyMovez*’ for the research project and co-creating the design and features of the app such as an avatar, game and social media platform called *Social Buzz*. At the end of 2016, six focus groups were conducted at two secondary schools ((*N* = 14; 12-14 y/o and *N* = 28; 12-14 y/o, respectively); with groups of boys or girls only and one mixed group at each school) to gather information about their social media use and to test the implementation of the social network functionality *Social Buzz*. All together, these focus group studies provided useful insights on youth’s attitudes concerning the design of the research application and practical information about the use of the *Wearable Lab*.

During Phase I, novel procedures and approaches to process and analyze data are explored. In addition, collaborations are set up, for example, to process photo data, analyze youth’s physical environment by connecting real-time data with Geographic Information System (GIS) measures, and analyze chat conversations from the *Social Buzz*. This also requires up-to-date safety and data management procedures according to legal and ethical standards. In sum, the *Wearable Lab* provides an innovative research methodology to collect data that increases the feasibility to implement and evaluate health campaigns.

## Methods/design

### Ethics statement

The research project is conducted according to the guidelines described in the Declaration of Helsinki and all procedures were approved by the ethical committee of the European Research Council (617253) and the Faculty Social Sciences, Radboud University, Nijmegen in the Netherlands (ECSW2014-100614-222).

### Design

The *MyMovez* project consists of a cross-sequential design, following two cohorts (8-12 and 12-15 y/o) over 3 years. Five waves of data are collected during the months February/March 2016 (w1), April/May 2016 (w2), June/July 2016 (w3), February/March 2017 (w4) and February/March 2018 (w5). Outcome measures involve social network characteristics, social media use, physical activity, beverage and snack consumption.

A power analysis was performed based on results from a previous cross-sectional longitudinal study that investigated energy balance behaviors among Dutch youth [35]. It was assumed that obesity inducing risk behaviors are present among approximately 40% of adolescents, and with a statistical significance level of .05 and 80% power, a sample size of 600 participants would be sufficient for the cross-sectional and longitudinal study. This sample size was also deemed appropriate for social network analyses, which require approximately 20-25 complete classroom networks. Assuming that Dutch school classes exist of an average of 25 kids, this would produce a sample between 500 and 625 students. Taking into account a conservative 40% attrition rate [36] we aimed to include 850 participants and oversampled the high school population because this age group is more likely to change schools or classes or drop out while followed during a period of three years. In the end, this led to recruitment of a sample of 953 participants.

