**Fig. 1 Fig1:**
[figure not shown]
Flow diagram of the MyMovez recruitment procedure

After obtaining (written) consent of the school’s principals, parents/legal guardians received an information letter and/or e-mail via the school announcing the project’s goals, planning, execution and safety procedures. Parents/legal guardians could enlist their child to the *MyMovez* study by giving consent on either a paper-and-pencil or digital form on the *MyMovez* website (www.mymovez.nl). The *MyMovez* website provides easily accessible information and updates about the project, team and progress (e.g., by a video illustrating how a day looks like for a participant, Q&A page, photos, and infographics). Researchers also visited schools to explain and promote the project in school classes and to hold information meetings for teachers, student mentors, and parent advisory boards.

Despite the schools’ and researchers’ efforts to promote the *MyMovez* project, parents/legal guardians did not always take notice of the research (e.g., the response rate at some schools was < 5%), resulting in disappointed pupils who wanted to participate on the day the research materials were handed out to their classmates. These pupils were given the opportunity to contact their parents/legal guardians to give their consent via the website or hand in a written consent form after the school break. In addition, pupils had the opportunity to participate during each of the following data collection waves, which has thus far resulted in different sample sizes for each data wave (in combination with drop out cases): *n* = 792 in Wave 1; *n* = 852 in Wave 2; *n* = 824 in Wave 3 and *n* = 671 in Wave 4. It is expected that the participation rates for Wave 5 (February 2018) will differ as well due to attrition and new participations.

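### Enrolling 850, or the 953 reached, does not leave the 600 set for the longitudinal study at the plan's own 40% attrition rate; that needs 1,000

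*Protocol article*

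**What the plan says.** The sample-size paragraph under Methods/design, Design, has four steps.

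- Power criterion: starting from an assumed prevalence of risk behaviour of about 40%, a 5% significance level and 80% power, the article concludes that "a sample size of 600 participants would be sufficient for the cross-sectional and longitudinal study".
- Network criterion: the same size is said to suit the social network analyses, "which require approximately 20-25 complete classroom networks". At 25 pupils per class, the article puts this at 500 to 625 pupils.
- Attrition: "Taking into account a conservative 40% attrition rate [36] we aimed to include 850 participants". The same sentence says that secondary-school pupils were oversampled because they are more likely to be lost.
- Result: "In the end, this led to recruitment of a sample of 953 participants".

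Under Recruitment of schools and participants, the article adds that pupils could enter at any later wave. It gives sample sizes of 792, 852, 824 and 671 for Waves 1 to 4; Wave 5 was still to come.

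**The concern.** The paragraph reads as one chain: 600 are needed, 40% may be lost, so 850 are sought, and 953 were found. A reader will conclude that the longitudinal study keeps its 600, and hence its 80% power, even if 40% drop out. An allowance for loss has to be made by dividing the required number by the share expected to remain. The step from 600 to 850 does not do that. If 40% were in fact lost, the longitudinal part would fall below the size on which its power statement rests, although the text says this loss was taken into account.

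**Working it through.** **Inputs, all from the Design section:** required size 600; attrition 40%; target 850; recruited 953; network range 500 to 625 pupils at 25 per class.

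**1. Where 850 could come from.** The article does not show the step, and neither of two candidates gives 850 exactly.

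- Multiplying the power-based size by 1 + 0.40: 600 × 1.40 = 840.
- Dividing the lower end of the network range by 1 − 0.40: 500/0.60 = 833.3, rounded up to 834.

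The upper end of the network range does not fit when divided: 625/0.60 = 1,041.7, so 1,042.

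**2. Enrolment needed to keep 600.** n/(1 − d) = 600/(1 − 0.40) = 600/0.60 = 1,000. The target is 150 below this and the recruited number 47 below.

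**3. What remains at 40% loss.**

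| Enrolled | Retained (× 0.60) | Short of 600 | Classes of 25 |
|---|---|---|---|
| 850 | 510 | 90 (15%) | 20.4 |
| 953 | 571.8, about 572 | 28 (4.7%) | 22.9 |
| 1,000 | 600 | 0 | 24.0 |

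**4. Attrition that each number covers.** The largest loss that still leaves 600 is 1 − 600/N.

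- N = 850: 1 − 600/850 = 29.4%.
- N = 953: 1 − 600/953 = 37.0%.

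**5. Check against the network criterion.** 510 and 572 both lie between 500 and 625, and 20.4 and 22.9 classes both lie between 20 and 25. On head count, that criterion is still met.

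**6. What 953 counts.** It is larger than each reported wave (792, 852, 824, 671), and late entry was open. That points to a cumulative count of everyone who ever joined. This is an inference; the article does not say it.

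**7. What cannot be checked.** The 600 itself cannot be rebuilt, because the article gives a prevalence, a significance level and a power but no comparison or effect size. The power at 510 or 572 therefore cannot be derived from the document.

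**The case against.** The strongest reply is that 850 was set from the network criterion. The attrition sentence directly follows the 500 to 625 range, and 500/0.60 = 834 is about as close to 850 as 840 is. On that reading the division was done correctly, and 510 retained pupils meet the stated minimum. This stands so far as it goes: the article does not establish that the authors multiplied by 1.40, and the network criterion holds. It does not rescue the 600, which the same paragraph sets for the longitudinal study and which 850 fails to protect at 40% loss on either reading.

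It is also fair to say that 40% is called conservative, that the gap from 953 is small, and that the Discussion foresees imputation of missing data. These points limit the consequence but do not make the stated allowance add up.

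Three stronger conclusions are tempting, and the documents do not support them.

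- A reader might set Wave 4 (671) against 953 and call the difference of 29.6% attrition. With open entry, one wave's sample against an apparently cumulative count is not an attrition rate. Nor does 671 show how many pupils were followed from Wave 1. All four reported waves exceed 600, so these counts do not threaten the cross-sectional claim.
- A reader might apply 40% to the 792 of Wave 1 and expect 475 completers. That ignores the late entry that the article openly describes.
- A reader might quote a power loss. With an assumed comparison of two equal groups at 40% and 29%, two-sided 0.05, power would be about 81% at 600, 79% at 572 and 74% at 510. The effect and the test are both assumptions, and the models listed under Strategy of analysis (actor-oriented, dyadic, multilevel, structural equation) are not a two-group comparison. The figures illustrate direction only.

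**Conclusion.** The concern holds as a sample-size statement that does not fit its own inputs. If 600 is required and 40% may be lost, 1,000 must be enrolled. The target of 850 leaves 510 and the recruited 953 leave about 572, so the stated allowance covers 29.4% and 37.0% loss respectively, not 40%. This rests only on the article's figures and on applying its attrition rate once to the number enrolled. Late entry means that an individual wave can still exceed 600.

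The failure is confined to the 600 for the longitudinal study. How 850 was reached remains unknown, and the effect on power cannot be sized from the document. Severity is moderate: the shortfall from the number actually recruited is 28 pupils, and no design or analysis decision has to change.

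**What to change.** Correct the attrition sentence in one of two ways: state that 600 after 40% attrition would need 1,000 enrolled, or state that 850 covers about 29% and 953 about 37% attrition. If 850 was derived from the classroom range, say so, and say that it does not secure the 600.

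Then restate the longitudinal power, or the detectable effect, at the retained number (510 for the target, 572 for the recruited sample), using the inputs of the authors' own power analysis.

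Finally, say whether 953 is the cumulative number ever enrolled, and give Wave 1 (792) alongside it.

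The cost is a few sentences and one rerun of an existing calculation. No extra participants are needed; the longitudinal statement becomes somewhat less favourable.
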